# Rehabilitation for children with chronic acquired brain injury in the Child in Context Intervention (CICI) study: study protocol for a randomized controlled trial

**DOI:** 10.1186/s13063-022-06048-8

**Published:** 2022-02-22

**Keywords:** Pediatric brain injury, Acquired brain injury, Goal-oriented, Family intervention, School, Community, Health care needs, Parenting, Online treatment, Telerehabilitation

## Abstract

**Background:**

Pediatric acquired brain injury (pABI) is associated with long-term cognitive, behavioral, social, and emotional problems, which may affect the quality of life, school, and family functioning. Yet, there is a lack of evidence-based community-centered rehabilitation programs for chronic pABI and these children do not systematically receive comprehensive rehabilitation. The Child In Context Intervention (CICI) study is a pragmatic randomized controlled trial (RCT) for children with chronic pABI, which aims to evaluate the effectiveness of an individualized and goal-oriented intervention targeting everyday functioning of the child and family.

**Methods:**

Children aged 6–16 years with MRI/CT-verified intracranial abnormalities will be included in the CICI study if they have persistent self- or parent-reported cognitive, emotional, and/or behavioral challenges 1 year or more after insult and attend school regularly. A total of 70 families will be randomized 1:1 to an intervention or a control group. The intervention consists of seven family sessions, one parent seminar, and four school sessions delivered over approximately 6 months. The parent seminar will be held in person, and the other sessions will mainly be video based. The children’s and families’ self-reported major challenges in everyday life will be targeted using SMART goals. Evidence-based strategies, when available, will be applied to achieve the goals, combined with psychoeducation. Goal attainment scaling (GAS) will be used to evaluate goal attainment. Data is collected at baseline and after approximately 6 and 9 months. External assessors are blinded to group allocation. Primary outcomes are parent-reported brain injury symptoms in children and parenting self-efficacy at 9 months of follow-up. Secondary outcomes include child-reported brain injury symptoms, quality of life, executive functioning in daily life, parent emotional symptoms, family functioning, and unmet family health care needs. A process evaluation will be conducted.

**Discussion:**

The current study provides an innovative approach to rehabilitation for children in the chronic phase of ABI and their families. This complex intervention may contribute to the development of evidence-based, high-quality rehabilitation for a large patient group, which is underrepresented in clinical research. It may also improve collaboration between specialized rehabilitation facilities, schools, and local health care services. Inclusion for the trial started in April 2021.

**Trial registration:**

ClinicalTrials.govNCT04798859. Registered on March 15, 2021

**Supplementary Information:**

The online version contains supplementary material available at 10.1186/s13063-022-06048-8.

## Introduction

### Background

Acquired brain injury (ABI) is inflicted after birth due to traumatic injury (e.g., falls, sports and traffic accidents, or assault) or non-traumatic insult (such as stroke, encephalitis, tumor, or hypoxia) and is the single most common cause of pediatric mortality and morbidity [1, 2]. Survivors frequently struggle with chronic cognitive, behavioral, social, and emotional problems, resulting in reduced everyday functioning and quality of life [3–5]. Pediatric ABI (pABI) often alters the pace and course of central nervous system maturation, affecting the whole life-course of the children involved [6, 7]. Thus, skills may fail to develop normally and challenges may become increasingly visible over time as societal demands and expectations increase [3, 6, 8]. Despite potentially severe long-term consequences, children with ABI do not currently receive systematic comprehensive rehabilitation in the chronic stage (more than 1 year after insult), resulting in unmet health care needs [3, 9–13] and placing them at risk for poor health outcomes and decreased quality of life. The lack of rehabilitation in the chronic stage leaves us with the paradox that symptom management for those whose lives are the most affected by the insult — children — is largely left to people without training in brain injury rehabilitation — their parents or caregivers. This is particularly unfortunate as having a child with ABI can negatively impact family functioning and parental mental health, which are in turn important predictors for the child’s functioning and well-being [14–17].

Similarly, teachers are left to manage the symptoms of pABI in the school setting, despite a lack of knowledge about pABI in schools [18, 19]. Alarmingly, many teachers of children with ABI may not even be aware that one of their students has suffered a brain injury/insult [20, 21]. A lack of collaboration between the health care and educational system [13, 22] may contribute to this. As a result, children and adolescents with ABI are under-identified for educational services and those who receive educational services are often under-served [23, 24]. To make matters worse, brain injuries in children tend to be “forgotten” over time in the educational system [25], even though many of these children and adolescents have persistent impairments and are in need of long-term follow-up [13, 23, 25, 26].

There is no solid volume of evidence-based treatment recommendations for cognitive rehabilitation after pABI, as research on pediatric brain injury rehabilitation is scarce. However, indirect interventions that aim to establish compensatory strategies and environmental adaptations to improve the children’s functional performance are recommended, while the sole use of so-called direct rehabilitation interventions, which focus on retraining of cognitive and functional impairment, holds less promise in the chronic stage [8, 27–35]. The few randomized controlled trials (RCTs) testing post-pABI parenting/family interventions indicate that problem-solving interventions are effective in reducing family conflict, enhancing parental functioning, reducing parental stress and psychological problems, and reducing internalizing and externalizing behavior in children and adolescents with ABI [36–41]. Despite the consensus that the complex interplay between brain injury symptoms, family function, and the child’s environment necessitates inclusion of the child’s family and school [29, 42], we are not aware of any RCTs that target both of these important environments in interventions directed towards chronic pABI. A recent evidence-based description of general rehabilitation describes effective rehabilitation as a complex, person-centered process with a range of activities, including but not limited to task practice, education, and psychosocial support, delivered by an expert multidisciplinary team working within the biopsychosocial model of illness [43]. Furthermore, as these children live with a wide variety of pABI-related difficulties, effective rehabilitation needs to be flexible and tailored to the individual’s needs, monitored, and modified if needed [43]. Brain injury interventions which fulfill these requirements have until now only targeted the adult population [44, 45], with research on pABI lagging behind.

The use of telerehabilitation, the delivery of rehabilitation services via information and communication technologies, expands the access to rehabilitation services and allows a higher frequency of rehabilitation services due to reduced cost and travel time [46] and thus holds promise for patients with pABI. In fact, it may be particularly suitable for patients with ABI as these are often severely affected by fatigue, which makes travel particularly burdensome. Furthermore, it offers a chance to increase the ecological validity of rehabilitation. Sometimes, maladaptive behavior or emotional reactions may be intense and highly prevalent in the home environment but hard to observe in the clinic. By allowing a more direct access to the home environment, telerehabilitation may be particularly suitable when tailoring interventions to everyday life, compared to rehabilitation delivered in a hospital setting. An effective way of doing so is by identifying and working towards individual rehabilitation goals for the child and parents, which ensures the family’s place at the helm of decision-making and increases their focus on the specific rehabilitation strategies [47, 48]. Involving parents in goal-oriented interventions has yielded promising results [8] and enhances adherence to the treatment program and the feeling of relevance that the treatment holds for the family [49].

The current study is modeled after two RCTs for adults with TBI [44, 45] and has been adapted to the pediatric brain injury population with a complex and innovative design to ensure a holistic approach.

### Objectives and hypotheses

The main aim of the Child in Context Intervention (CICI) is to enhance everyday functioning of children with ABI in the chronic stage in the home and school environment and to improve family life. We expect that the intervention, compared to treatment as usual (TAU), will result in reduced parent-reported brain injury symptom severity in children (H1) and improved parental self-efficacy (H2). We furthermore expect that the intervention will result in lower levels of child-reported brain injury symptoms (H3), fewer unmet health care needs in the families (H4), and improved everyday executive functioning (H5) and quality of life for children (H6). Improved family functioning (H7), parental mental health (H8), and finally, reduced child- and parent-reported severity of the individually defined target outcome areas (main pABI-related problems in daily life) (H9) are also expected. Group differences will be evaluated approximately 6 months and 9 months after baseline, with 9 months (T3) being the primary endpoint. In the treatment group, we expect to see positive goal attainment (H10), and high satisfaction of the participating stakeholders (children, parents, teachers, and rehabilitation professionals) with the intervention program (H11).

## Methods

### Study design

The present study is a two-group RCT with a mixed-methods design. A total of 70 children and their families will be randomly assigned to the CICI intervention or control group. The intervention team includes the child, parents (in an assumed minority of cases only one parent), the child’s teacher, a therapist, and a special education specialist. These will work in close collaboration towards the goals of the participating child and family. Most sessions, except for the parent seminar, will be delivered by videoconference, thus reducing the burden of travel and time for the families and therapists. Assessment will be performed at baseline (T1), approximately 6 months later (T2), and 9 months after baseline (T3). The total duration of participation is 9 months. The day of the baseline assessment is regarded as the time point for inclusion. When preparing this protocol, we used the SPIRIT reporting guidelines [50] and a figure with the standard protocol items (SPIRIT) is presented in Fig. 1. The SPIRIT checklist is available as an additional file (Additional file 1).

**Fig. 1 Fig1:**
[figure not shown]
Standard Protocol Items: Recommendations for Interventional Trials (SPIRIT)

Potentially eligible families will be invited by letter and screened for inclusion by phone, following an established screening protocol. All three therapists conduct the screening, as it is not feasible for one person to follow up all the phone calls. The baseline assessment (T1) will include an interview with at least one parent including anamnestic information and current use of healthcare services, a brief cognitive screening of the child with the Similarities and Matrix subtests from the Wechsler Intelligence Scale for Children, Fifth edition (WISC-V) [51] for estimating intellectual ability and questionnaires for assessing (1) executive functions of the child in daily life [52], (2) health-related quality of life of the child and brain injury symptoms [53, 54], (3) emotional symptoms of the parents [55, 56], (4) parenting self-efficacy [57], (5) family functioning [58], and (6) unmet health care needs [59] (Table 1). The baseline assessment will also include identification of three main problems in daily life, related to the child’s ABI. The main problems in daily life will be reported by children, according to their age and cognitive functioning, and their caregivers, and rated individually on a 5-point Likert scale according to the level of their burden. The families in the intervention group will rate how helpful they expect the intervention to be on a scale from 1 to 10 during sessions 1 and 3. The intervention was developed according to the UK Medical Research Council framework [60] and also complies with the updated framework, as the CICI study strives to be a solution for real-world practice [61]. The CICI study will be carried out in close collaboration between the specialized health care system, Statped (the Norwegian Service for Special Needs Education), teachers, and local rehabilitation services. Senior scientists will oversee 10% of family sessions to ensure adherence to protocol. Due to the small sample size and as we are documenting dates and times of the intervention, an external data protocol committee is not judged to be necessary.

**Table 1 Tab1:** Outcome measures, respondents, and time points

Outcome measure topic	Name of measure	Respondents	Time points
Brain injury symptoms	Health and Behavior Inventory (HBI) [54]	Parents, children from 7 years	T1, T2, T3
Parenting self-efficacy	Tool to measure Parenting Self-Efficacy (TOPSE)^1^ [57]	Parents	T1, T2, T3
Executive functioning at home and in school	Behavior Rating Inventory of Executive Function 2 (BRIEF-2) [52]	Parents, teachers, children from 11 years	T1, T2, T3
Children’s quality of life	The Pediatric Quality of Life Inventory (PedsQL)^1^ [53]	Parents, all children	T1, T2, T3
Unmet healthcare needs of the family	Family Needs Questionnaire (FNQ-P) [59]	Parents	T1, T2, T3
Parents’ symptoms of depression	A brief depression severity measure (PHQ-9) [55]	Parents	T1, T2, T3
Parents’ symptoms of generalized anxiety	A brief measure for assessing generalized anxiety disorder (GAD-7) [56]	Parents	T1, T2, T3
Main ABI-related problems in daily life	Likert scale 1–4	Parents, all children	T1, T2, T3
Participants’ evaluation of the intervention	CICI Evaluation (custom made for the CICI study)	Parents, all children, teachers, therapists	T2
Goal attainment scaling	The goal stairs 1–5 (custom made for the CICI study)	Families with therapists	T2

^1^Different versions are applied for different age groups

A feasibility study, using qualitative and quantitative methods, was applied to evaluate inclusion criteria, feasibility of the intervention, the technical solution, adherence to the study protocol, the acceptability of the intervention to children, parents and therapists, mechanism of action, and outcome measures [62]. The current manuscript describes the final study protocol after feasibility testing.

### Study setting

Baseline assessments will be conducted at Sunnaas Rehabilitation Hospital ([name]), which is one of the largest rehabilitation hospitals in Northern Europe and the owner of the present study. Intervention sessions will primarily be delivered by videoconference, while the parent seminar will be held at Sunnaas Rehabilitation Hospital or a conference center in the same region. The study is conducted in close collaboration with Oslo University Hospital and Statped, the Norwegian Service for Special Needs Education.

### Participants

The study population will consist of children with ABI with persistent self- or parentally reported insult-related cognitive, emotional, behavioral, and/or social challenges.

*Inclusion criteria are:*
School-aged (6–16 years) children with clinical ABI diagnosis and CT/MRI-verified insult-related intracranial abnormalities or loss of consciousness post-insult and verified neurological symptoms in cases where MRI could not be administered. We anticipate to include children with TBI, cerebrovascular incidents, anoxia, encephalitis, brain tumors, and brain injury caused by radiation.Time since insult at least 1 year.The children report ABI-related cognitive, emotional, behavioral, and/or social problems that affect everyday functioning and/or participation in activities with family, friends, school, and/or community, and/or the parents report these symptoms on behalf of the children.The children attend school regularly, with or without insult-related adaptations.The family is able to actively participate in goal-oriented work, including having Internet access and speaking sufficient Norwegian. An exception can be made for parents who speak English but are able to understand and read study-related information in Norwegian.

*Exclusion criteria:*
Children with severe pre- or comorbid neurological or neuropsychiatric disorders that would confound assessment and/or treatment outcomes.Children with brain tumors or cancer in active treatment or at great risk of relapse (unstable condition).Children with severe psychiatric illness or injuries so severe that they are in institutionalized care most of the time.Parental severe psychiatric illness, drug abuse, or indications of a history of or risk of domestic violence.

### Outcome measures

The primary outcome measures assess parent-rated severity of children’s brain injury symptoms (Health and Behavior Inventory, HBI) [54] and parenting self-efficacy (Tool to measure Parenting Self-Efficacy, TOPSE) [57] at T3. See Table 1 for an overview of all assessment measures, respondents, and time points.

### Randomization and allocation concealment

Participants will be randomly allocated in a 1:1 ratio to either the intervention group or the control group after completing the baseline (T1) assessment. A Web-based block randomization will be generated by an independent statistician prior to trial start-up to ensure randomization and complete allocation concealment. The allocation will be performed in Viedoc™ (Viedoc Technologies AB, Uppsala, Sweden), the electronic data capture system used in this study (see below). The allocation sequence can be accessed by neither the therapists nor the outcome assessors, only by the study principal investigator. Randomly generated block sizes will be applied. Outcome assessors blinded to group allocation will interview participants and collect information on target outcome areas (main pABI-related problems in daily life) at T2 and T3. For apparent reasons, blinding of participants and interventionists is not possible, but researchers will be blinded to group allocation in the final database, as the participants will be provided with new ID numbers.

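### The allocation sequence is described as completely concealed, yet the principal investigator may read it, with no stated limit on when or why

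*Protocol article*

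**What the plan says.** All but one of the relevant statements stand in the Protocol article under Randomization and allocation concealment.

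- Origin of the list and the property claimed for it: "A Web-based block randomization will be generated by an independent statistician prior to trial start-up to ensure randomization and complete allocation concealment".
- Timing and ratio: "Participants will be randomly allocated in a 1:1 ratio to either the intervention group or the control group after completing the baseline (T1) assessment".
- System: "The allocation will be performed in Viedoc".
- Blocks: "Randomly generated block sizes will be applied".
- Access: "The allocation sequence can be accessed by neither the therapists nor the outcome assessors, only by the study principal investigator".
- Blinding at analysis: "researchers will be blinded to group allocation in the final database, as the participants will be provided with new ID numbers".

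The remaining statement is under Study design, in the text after Fig. 1, and concerns who screens: "All three therapists conduct the screening, as it is not feasible for one person to follow up all the phone calls".

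The article does not restrict the principal investigator's access to a purpose, to emergencies, or to entries already assigned. It also does not say whether the principal investigator decides on eligibility, schedules T1 visits, triggers the allocation or analyses the data.

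**The concern.** Concealment means that nobody who can affect which family enters, or in what order, knows the next assignment. Here the list exists before the first family is enrolled, and the person leading the trial may open it. Having an outside statistician generate the list is meant to keep it away from the study team; access by the team's leader gives part of that protection away.

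Two features of this trial make concealment worth guarding.

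- Several entry criteria under Participants call for judgement: whether a family can take an active part in goal-directed work, and whether a coexisting disorder is serious enough to distort assessment or outcome. Borderline cases are the kind that get referred upwards.
- Other protection against bias is limited. Both primary outcomes, the parent-rated HBI and the TOPSE, come from parents who know their group. The blinded assessors collect the family's main problem areas, not these two scales.

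**Working it through.** The plan gives no figure on this point and none is needed. The check is whether the statements fit together.

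1. **When is the list knowable?** It is generated before start-up, so every entry for the planned 70 families exists while recruitment runs.

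2. **Who can read it?** The access sentence excludes therapists and outcome assessors and admits the principal investigator. It sets no condition of time or purpose, so as written it covers entries not yet assigned.

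3. **Do the other safeguards cover this?** Random block sizes stop someone from inferring the next assignment from past ones. Allocation in Viedoc after T1 stops an ordinary user from seeing an assignment early. Neither helps against a person who can read the list itself.

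4. **Is there a stated need for the access?** None is given. Families and therapists know the treatment anyway, so emergency unblinding does not require it.

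5. **Does the access reach the people who enrol?** On the text, no. The three therapists screen, and they are denied the sequence. The article gives the principal investigator no enrolment task. It also does not state that the principal investigator is kept out of eligibility decisions or scheduling.

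6. **Does it defeat the blinding of researchers?** That statement covers only the final database, where participants carry new ID numbers. The original sequence would undo it only if the principal investigator worked on that database and could also link old to new numbers or recognise families. The article states neither condition.

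Steps 1 to 4 show that the stated arrangement does not match the stated property. Steps 5 and 6 show how far that goes: to the word complete, and not to a demonstrated breach.

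**The case against.** The strongest reply is that concealment concerns those who enrol. The screeners work by telephone to a set screening protocol and cannot see the list, and nothing places the principal investigator in the enrolment chain. The article also condenses a fuller protocol, so its silence on the principal investigator's duties is no evidence that those duties include enrolment. This stands in full against any claim that assignments were, or will be, steered. It does not rescue the claim of complete concealment, because the article itself states that one member of the study team can read the sequence.

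A second reply concerns the consequence. A reader might infer that the trial is open to selection bias that no analysis can remove. That is too strong. T1 is measured before allocation, and under Statistical analyses the primary contrast is a time by group interaction over all assessments. An imbalance in baseline level would largely drop out of that contrast; steering on expected change would not.

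A reader might also infer that the access contradicts the blinding of researchers. Step 6 of the working shows why the text does not support that. What remains is an open question about whom that blinding covers.

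**Conclusion.** The point holds in a limited form. The article claims complete concealment for a pre-generated sequence and, in the same section, gives the principal investigator access to it without limit. The two statements need to be reconciled. No actual breach is shown.

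The size is qualitative: as written, one person can read every unassigned entry. A reader might want this as a bias in SD units, but the documents do not support a figure. If k families in an arm of 35 (70/2) were steered and differed by d SD in prognosis, the arm mean would shift by k × d / 35. With k = 1 and d = 0.5 that is 0.5/35 = 0.014 SD, and with k = 3 and d = 1 it is 3/35 = 0.086 SD. Against the planned effect of 0.8 these are 0.014/0.8 = 1.8% and 0.086/0.8 = 10.7%. Both k and d are assumptions, so the range shows only how far the answer depends on them. The conclusion does not rest on it.

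The verdict assumes that the access sentence means what it says, that is, access to the sequence and not only to assignments already made. If the latter was meant, correcting the wording settles the matter.

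**What to change.** - Remove the principal investigator's access to unassigned entries for as long as recruitment runs. Keep the list with the independent statistician and inside Viedoc.
- Release each assignment singly, only after that family's T1 is complete. This agrees with the timing already planned.
- Report any period in which the access existed, so that readers can judge the families enrolled in that time.
- If some access has to stay, state its purpose and timing, and state that the principal investigator takes no part in eligibility decisions or in scheduling T1.
- Say whether the principal investigator is among the researchers blinded in the final database.

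The cost is a few sentences in the protocol and a change in who may open the list. The article does not describe how the access is set up, so it is an assumption that a change of user rights is enough. Sample size, visits and analysis are unaffected. The Trial status section expects recruitment to run until spring 2023, so a change made before then would protect the assignments still to come; after that, only the reporting and the clarification remain.
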